### Randomization procedure

Included study participants are randomly assigned by block randomization to one of four groups in block sizes of 160 (Table 3). Stratified randomization was not used. Prior to the study start, an assistant not involved in the project prepared 800 opaque, sequentially numbered sealed envelopes with cards marked; 1 (massage), 2 (exercise therapy), 3 (massage and exercise therapy) or 4 (advice) indicating one of the four treatment arms. The number sequence was attained by placing 160 (40 of each numbered fold cards) in an urn, mixing them before placing them, one at the time, into numbered opaque envelopes. Study participants are sequentially numbered by the study assistant before the initial visit, and receive the assigned set of documents, including the envelope, with the corresponding number when they come to the study center. The unmasking is performed by the therapist after the baseline B questionnaire is filled in and after the physical examination and second- step exclusions, so that the study administrator, the therapist and the study participant are blinded to the group assignment until after all study participant baseline data have been collected.

**Table 3 Tab3:** Interventions

Treatment arm	Description	Time per treatment	Number of sessions	Duration
Massage (A)	Massage will be applied to the neck, thoracic spine area, TMJ^a^ (if indicated) and chest (including the chest muscles)	30 min (in total 45 min session)	up to 6	6 weeks
Exercise therapy (B)	Self-mobilization exercise (gentle controlled movement) of the neck and shoulder joints, including neck retraction, extension, flexion, rotation, lateral bending motions, and scapular retraction) and strengthen exercises	30 min (in total 45 min session)	Up to 6	6 weeks
Massage and Exercise therapy (C)	Combination of A + B	50 min, 25 min of each (in total 60 min session)	Up to 6	6 weeks
	Massage treatment followed by physical exercise.			
Advice to stay active (D)	Support and advice on staying active and on pain coping strategies, according to guidelines and evidence-based reviews	30 min	Up to 3	6 weeks

^a^TMJ: temporomandibular joint

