### Baseline

Baseline clinical and demographic data, as well as potential prognostic factors for neck pain, are measured using two baseline questionnaires administered before medical examination, inclusion and randomization. The first baseline questionnaire (A) is completed by telephone interview a maximum of  7 days before the first visit to the study clinic by a research assistant. Study participants fill in the second baseline questionnaire (B) at the study clinic before they meet the therapist at the first visit and before the randomization. The baseline factors are sex, age, education, pain and disability in neck and back [31, 33–35], duration of neck pain, previous episodes of neck pain, health-related quality of life (EQ-5D) [36–38], psychological distress (GHQ-12) [39], smoking, physical exercise, height, weight, sick leave, physical demands at work [40] and job strain [41, 42]. An overview of the Baselines A and B assessment is presented in Table 4.

**Table 4 Tab4:** Baseline assessments

Baseline	Contains	Instruments
Baseline A (phone call maximum 7 days before first visit)		
General Information [39, 62]	Informed consent for the enrolment in the study	
	Sex	
	Housing and housing environment	
	Education	
	Occupational class [63]	
	Previous experience from massage therapy and/or personal trainer (YES/NO)	
Neck pain	Pain intensity and disability related disability in neck [35]	Chronic Pain Questionnaire
	Duration of neck pain	
	Previous episode of neck pain	
Baseline B (paper questionnaire at first visit)		
Lifestyle [36, 39]	Height and weight	
	Cigarette smoking [64]	
	Leisure time and occupational physical activity [65]	
	Physical demands at work [40, 41]	
General health	Self-rated health [66]	
	Health related quality of life [38]	EQ-5D
	Psychological distress [67]	GHQ-12
	Emotional well-being	
	Anxiety, worry, anguish [68]	
	Expectation of recovery	
	Sleeping problems [42]	
	Persistent fatigue	
Chronic diseases	Diabetes	
	Cardiovascular disease	
	Chronic obstructive pulmonary disease	
	Psoriasis	

As part of the physical examination study participants undergo a number of clinical neck tests in order to rule out cervical radiculopathies [43], to evaluate the range of motion of the cervical and thoracic spine and to assess the deep cervical muscle function [43–47]. A flow chart over the study procedure is presented in Fig. 1.

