### Statistical analyses

The comparison of the effect between the groups statistical analyses will be performed using an “*intention to treat”* principle aimed at analyzing participants in the group to which they were originally assigned and to keep the dropouts in the assigned group no matter what the reason [57]. To estimate the impact of missing responses, sensitivity analysis for the primary outcomes will be performed using multiple imputation [58]. Changes in mean scores at follow-up compared with baseline, and differences in changes between groups will be calculated by unpaired t-test. To compare the groups regarding the dichotomized outcomes, relative risks (RR) and risk differences (RD), together with corresponding 95 % confidence intervals (CI), will be calculated. Baseline factors that differ between the treatment groups will be considered with regard to their potential confounding effect by means of Mantel Haenszel’s method [59]. If adjustment is needed, the Cox proportional Hazard model will be used.

Generalized estimating equations (GEE) will be performed to analyze the effect on the primary outcome (pain and disability) over the total follow-up time, including the automated text messages (SMSes). The GEE method extends standard regression analysis, taking into account the covariance between repeated measurements of pain and disability [60, 61].

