### Limitations

One of the major methodological difficulties inherent to studies evaluating physical interventions is blinding of therapists and study participants. The nature of the interventions makes it impossible to blind the care provider and difficult to blind the study participant.

Unmasking will be performed by the care provider after the physical examination, the second-step exclusions and the data collection with baseline questionnaires, so the study administrator, the therapist and the study participant all will be blind to the group assignment until after all baseline data is collected. We will measure study participant’s previous experience of the interventions, expectation of recovery and expectation of the importance of the allocated therapy for the recovery (just after the unmasking and before the intervention starts). In an attempt to minimize bias from potential differences in expectations of recovery between the four groups will test the potential confounding effects of these factors in the statistical analyses.

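### Covariate adjustment depends on observed baseline imbalance, so it can omit baseline pain and disability and leaves the adjusted model to be chosen after the data are seen

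*Protocol article*

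**What the plan says.** The Statistical analyses section of the protocol article sets out three kinds of effect analysis. For mean scores, "differences in changes between groups will be calculated by unpaired t-test". For the dichotomised outcomes, relative risks and risk differences are given with 95 % confidence intervals. For the whole year including the text messages, "Generalized estimating equations (GEE) will be performed to analyze the effect on the primary outcome (pain and disability) over the total follow-up time". No covariate is named for any of them.

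Covariates enter in two steps. First, "Baseline factors that differ between the treatment groups will be considered with regard to their potential confounding effect", with Mantel-Haenszel as the tool. Second, "If adjustment is needed, the Cox proportional Hazard model will be used". The section does not define what counts as a difference or as a need.

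Three other sections bear on this:

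- **Baseline:** "potential prognostic factors for neck pain, are measured using two baseline questionnaires administered before medical examination, inclusion and randomization". The material for a fixed covariate set is therefore collected in time.
- **Randomization procedure:** "Stratified randomization was not used".
- **Limitations:** previous experience of the interventions, expectation of recovery and expectation of the allocated therapy are named, and the team "will test the potential confounding effects of these factors in the statistical analyses". The last of these is asked after the participant has learned the allocation.

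**The concern.** In a properly randomised trial any baseline difference between arms is chance. Whether a factor deserves adjustment depends on how strongly it predicts outcome, and the size of the observed difference says nothing about that. A strongly prognostic factor that happens to be balanced fails the first step, and the precision it would have given is lost.

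The factors most likely to be lost this way are the baseline pain and disability scores. The primary outcomes depend on them by construction. The exclusion criteria admit a mean pain score of 2 and a mean disability score of 1, and response is a two-step or one-step decrease. A participant entering at either limit can respond only by scoring zero on all three items.

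The second matter is discretion. A Mantel-Haenszel check ordinarily compares the crude with the stratified treatment effect, so the decision to adjust is taken with outcomes by arm in view and with no stated threshold.

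**Working it through.** **The plan's own figures.** The article gives no figure for the adjustment rule. Its one power statement (above 80 % with 600 participants for RR 1.2 to 1.3) concerns the responder outcomes and gives no control rate, so it cannot be confirmed. With 150 against 150 and an assumed two-sided 5 % level, RR 1.3 gives 75 % power at a control rate of 0.50 and 85 % at 0.55. The point below does not depend on it.

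**How often something will differ by chance.** Assume that a difference means p < 0.05 in one comparison per factor and that factors are independent. The expected number is 0.05k, and the chance of at least one is 1 − 0.95^k. The text of the Baseline section lists about 18 factors, and Table 4 brings the count to about 25 or more.

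| k | Expected | At least one |
|---|---|---|
| 18 | 0.05 × 18 = 0.9 | 60 % |
| 25 | 0.05 × 25 = 1.25 | 72 % |
| 30 | 0.05 × 30 = 1.5 | 79 % |

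Four arms give six pairwise comparisons, which adds opportunities. These are chances that a factor is examined. They are not chances that it is adjusted for.

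**Precision.** Inputs are 150 per arm (600 over four equal arms), an assumed effect of 0.3 SD, and an assumed correlation ρ between baseline and follow-up scores with equal SDs of 1.

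- The variance of a change score is 2(1 − ρ). The residual variance under ANCOVA is 1 − ρ². Their ratio is (1 + ρ)/2, that is 0.65, 0.75 and 0.85 at ρ = 0.3, 0.5 and 0.7.
- At ρ = 0.5 the change-score SE is √(2 × 1/150) = 0.1155, so 0.3/0.1155 = 2.60 and power is Φ(2.60 − 1.96) ≈ 74 %. The ANCOVA SE is √(2 × 0.75/150) = 0.10, so 0.3/0.10 = 3.0 and power is Φ(3.0 − 1.96) ≈ 85 %.

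A simulation of 10,000 runs per setting added the rule itself: ANCOVA if the baseline score differed at p < 0.05, otherwise the change-score t-test.

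| ρ | Power: change-score t-test | Power: rule | Power: fixed ANCOVA | Type I error: rule | Type I error: fixed ANCOVA |
|---|---|---|---|---|---|
| 0.3 | 59 % | 60 % | 77 % | 4.2 % | 5.2 % |
| 0.5 | 73 % | 74 % | 84 % | 4.4 % | 5.2 % |
| 0.7 | 92 % | 92 % | 95 % | 4.3 % | 4.6 % |

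The rule recovers almost none of the precision that fixed adjustment gives. The simulation adjusts whenever the baseline score differs. The protocol's second step could only make adjustment rarer.

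**Type I error given an imbalance.** For a covariate with correlation 0.5 with the outcome and a baseline imbalance of z standard errors, the unadjusted rejection rate under no effect is P(|N(0.5z, √0.75)| > 1.96).

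| z | 0 | 0.5 | 1 | 1.5 | 1.9 |
|---|---|---|---|---|---|
| Rejection rate | 2.4 % | 3.0 % | 4.8 % | 8.2 % | 12.2 % |

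The change score is not exempt. At ρ = 0.5 its covariance with baseline is ρ − 1 = −0.5 and its SD is 1, so it correlates −0.5 with baseline.

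**The case against.** The strongest defence is that the rule has two steps. A factor that differs is only considered, and one unrelated to outcome would barely move a Mantel-Haenszel estimate. This stands. A reader might infer from the 60 to 79 % range that irrelevant factors will probably be adjusted for, and the text does not support that. The threshold and the independence behind those figures are also assumptions. Table 4 includes GHQ-12, anxiety, sleep and fatigue, which are surely correlated.

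Second, baseline pain and disability are not ignored, since responder status and the t-test are both built on change from baseline. This is true, but neither is adjustment. A change score fixes the coefficient of baseline at 1 and keeps the dependence shown above.

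Third, the Limitations section names expectation and experience factors in advance. That also stands, so it would be wrong to say that only factors which happen to differ are ever looked at. Those factors are still to be tested for confounding and are not fixed as covariates. They do not include baseline pain or disability, and one is recorded after unmasking, when allocation may already have affected it.

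Fourth, a reader might infer from the 8 % and 12 % rates that the plan inflates type I error. They hold only given imbalances of 1.5 and 1.9 standard errors. For smaller imbalances the rate is below nominal, it averages 5 % over randomisation, and the simulated rule came out slightly conservative. Lack of stratification does not alter this: the unadjusted comparison remains valid.

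Finally, covariate lists are often left to a statistical analysis plan. Here, however, the protocol states a rule, and the rule can be judged as stated.

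**Conclusion.** The point holds as a matter of precision and prespecification. It is not one of validity. The protocol selects covariates on observed imbalance, leaves both steps undefined, and so can omit the baseline score from every effect model.

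For a continuous score the cost is about 17 percentage points of power at ρ = 0.3, 10 at 0.5 and 3 at 0.7. This rests on 150 per arm, no dropout, an effect of 0.3 SD, a two-sided 5 % level, and p < 0.05 as the meaning of a difference. None of the last four is stated in the article. The figures do not carry over to the dichotomised outcomes, for which no gain was computed. Discretion over many candidate factors was not simulated either, so its effect on error rates is unknown. Nothing in the documents supports a claim of overall type I inflation.

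**What to change.** Replace the rule in Statistical analyses with a fixed primary specification:

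- Every effect model (scores, responder RR and RD, GEE) adjusts for the baseline value of the outcome score and for neck pain duration (30 to 90 against more than 90 days), whatever the observed balance. Table 2 lists the text messages only under follow-up, so the baseline CPQ pain or disability score can serve for those items.
- Scores are analysed by ANCOVA in place of the t-test on changes.
- Responder outcomes use a binary regression that yields both measures with valid standard errors. One choice is logistic regression standardised over the trial population, with delta-method intervals. This replaces the Cox sentence.
- The adjusted estimate is declared primary, and the unadjusted RR and RD are shown as supportive.
- Imbalance-driven adjustment is a sensitivity analysis only, restricted to variables measured before allocation is revealed. Expectation recorded after unmasking is therefore not used as a covariate.

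The cost is a revised paragraph and slightly more modelling. Both covariates are already in Baseline A. The article reports recruitment as ongoing and places the analyses in 2017 to 2019, so on its own timeline the change can be fixed before outcomes are compared by arm.

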## Methods/Design

### Study design

The study design is a randomized controlled trial. At least 600 study participants with long-lasting or subacute neck pain will be randomized to one of four treatment arms. To be able to discuss the balance between effectiveness and harm in the treatment arms, adverse events will be monitored with a questionnaire after each visit [24].

A blinded trial is not possible in this case because of the character of the interventions. Attempting to compensate for the lack of blinding, we measure study participant’s previous experiences of the interventions. Furthermore, we ask them about their expectations of recovery before randomization allocation and about their expectations of treatment effect right after finding out the treatment to which they have been allocated.

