### Sample size

Power analyses based on the primary outcomes have been performed to determine the sample size. A total of 600 participants indicated a power of >80 % to detect a relative risk of 1.2 to 1.3 for a clinically important improvement in pain and disability; a two-step decrease in the mean pain intensity score (CPQ; NRS 0 to 10) and a one-step decrease in mean pain-related disability score (CPQ; NRS 0 to 10) when baseline is compared to the values at follow-up. These calculations are based on the differences in effect between manual therapy and advice to stay active detected in our previous trials, which are 16 to 27 % depending on the length of the follow-up time [26, 27].

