### Follow-up

Study participants are followed by web-based questionnaires 7, 12, 26 and 52 weeks after inclusion in the trial and by weekly automated text messages (SMSes) [48–51].

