#### Primary outcomes

The primary outcomes are pain and disability, measured by a slightly modified Chronic Pain Questionnaire (CPQ) (4-week recall period instead of 6 months) [31, 33–35] with six items on a numerical 11-point rating scale and one item on the number of disability days of pain and disability. Three items are used to rate the pain (the current pain, the worst pain experienced during the preceding 4 weeks, and an average of the pain during the preceding 4 weeks). A pain score will be constructed from the mean of these three items. Three items are used to rate disability and concern to what degree pain “interfered with your daily activities,” “changed your ability to take part in recreational, social, and family activities” and “changed your ability to work (including housework)” in the past 4 weeks. The disability score will be the mean of these three items. On the basis of these scales, two dichotomized outcomes will be defined based on what is considered to correspond to a clinically significant improvement: a two-step decrease in pain intensity and a one-step decrease in pain-related disability when baseline is compared to the values at follow-up [52].

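### The Cox model named for adjusted analyses does not fit yes/no outcomes at fixed weeks: unless constant time, Breslow ties and robust variance are used, the adjusted relative risk has too-wide intervals or is not the stated relative risk

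*Protocol article*

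**What the plan says.** The Primary outcomes section builds mean pain and disability scores from the Chronic Pain Questionnaire and then states that "two dichotomized outcomes will be defined based on what is considered to correspond to a clinically significant improvement": a fall of two steps in pain and of one step in disability, comparing baseline with follow-up. The Follow-up section fixes the times: "Study participants are followed by web-based questionnaires 7, 12, 26 and 52 weeks after inclusion in the trial". No event time or censoring rule is defined for either outcome.

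The Statistical analyses section compares the groups on these outcomes by "relative risks (RR) and risk differences (RD), together with corresponding 95" % confidence intervals. Baseline factors that differ between groups are examined for confounding by the Mantel-Haenszel method. Then comes the sentence at issue: "If adjustment is needed, the Cox proportional Hazard model will be used". Nothing is said about the time variable, the handling of ties or the variance estimator. The weekly text messages are assigned to generalized estimating equations, so they do not supply an event time for the Cox model.

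**The concern.** A Cox model estimates a hazard ratio from event times, and these outcomes have none: each is a status read at a fixed questionnaire. Analysts sometimes give everyone the same follow-up time so that the Cox coefficient becomes a log relative risk. That device is sound only with suitable tie handling and a robust variance. With model-based variance, the model treats the number of improved participants as a Poisson count, which overstates the uncertainty when improvement is common.

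Two primary outcomes are affected whenever adjustment is triggered. That is a realistic prospect: Table 4 lists many baseline factors, there are four arms without stratification, and the Limitations section commits to testing expectations as confounders. A real effect could then appear clearly in the unadjusted relative risk and vanish in the adjusted one for no reason other than the variance formula. The adjusted analysis would also have no counterpart to the planned risk difference.

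**Working it through.** **Inputs.** The article gives 600 participants in four arms (Study design) and equal allocation, from the urn of 160 cards with 40 per arm (Randomization procedure), so 600/4 = 150 per arm. The Sample size section says "A total of 600 participants indicated a power of >80" % for a relative risk of 1.2 to 1.3. A two-sided 5 % level is assumed from the 95 % intervals. No response rate is given for any arm, so control rates are an assumption throughout.

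**Step 1: the plan's own figure.** Without a control rate the stated power can only be solved backwards. With p̄ the mean of the two rates,

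power = Φ{[|p1 − p0| − 1.96·√(2p̄(1 − p̄)/n)] / √[(p1(1 − p1) + p0(1 − p0))/n]}.

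At n = 150, 80 % power needs a control rate of at least 52.5 % (versus 68.3 %) for a relative risk of 1.3, and 69.0 % (versus 82.7 %) for 1.2. If the lower figure of 16 % quoted from previous trials is read as an absolute difference, then at a relative risk of 1.3 the control rate is 0.16/0.3 = 53.3 %, against 69.3 %. Power is then about 81.5 %, compatible with the text.

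**Step 2: what constant-time Cox estimates.** Let a and c be the numbers improved in two arms of n each, all with the same time. With Breslow ties the log partial likelihood is aβ − (a + c)·log(n·e^β + n).

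- Setting the derivative to zero gives e^β = a/c, which is the relative risk.
- The information at that point is ac/(a + c), so the model-based variance of the log relative risk is 1/a + 1/c.
- The binomial variance is 1/a − 1/n + 1/c − 1/n.

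With equal arms the ratio of interval widths on the log scale is √[(1/p1 + 1/p0)/(1/p1 + 1/p0 − 2)], whatever n is.

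**Step 3: one worked case.** Take 98/150 versus 75/150 (about 65 % versus 50 %), relative risk 98/75 = 1.31.

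- Model-based standard error: √(1/98 + 1/75) = 0.153, interval 0.97 to 1.77.
- Binomial standard error: √(1/98 + 1/75 − 2/150) = 0.101, interval 1.07 to 1.59.
- Ratio 0.153/0.101 = 1.52. Poisson regression with robust variance gives 0.101.

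**Step 4: range over assumed control rates.** Excess width on the log scale under model-based variance:

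| Control rate | RR 1.2 | RR 1.3 |
|---|---|---|
| 30 % | +22 % | +23 % |
| 40 % | +33 % | +35 % |
| 50 % | +48 % | +52 % |
| 55 % | +58 % | +63 % |
| 60 % | +70 % | +76 % |
| 70 % | +106 % | +119 % |

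At the lowest rates that give 80 % power (Step 1) the excess is 57 % (RR 1.3) and 101 % (RR 1.2).

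**Step 5: cost in power.** In 200,000 simulated two-arm trials without covariates, 150 per arm, 53.3 % versus 69.3 %, the nominal 95 % interval covered the true value 99.8 % of the time under model-based variance and 95.1 % under binomial variance. Power was 38 % and 82 % respectively.

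**Step 6: other ways of carrying out the sentence.** At 50 % versus 60 % (relative risk 1.20), Breslow ties give 1.20 and Efron ties 1.30, while exact or discrete ties move towards the odds ratio of (0.6/0.4)/(0.5/0.5) = 1.50. The hazard ratio implied by the same two rates is ln(0.4)/ln(0.5) = 1.32. In every version the coefficient is a log ratio and gives no risk difference directly.

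**The case against.** The strongest reply is that the sentence can be carried out correctly. Constant time with Breslow ties and robust variance returns the relative risk with the right interval: at 50 % versus 60 % the robust and binomial standard errors are both 0.1054. The article neither adopts nor excludes this version, and such settings may sit in a fuller document that is not shown. This stands. It rules out the reading that the adjusted intervals will certainly be wrong. It does not remove the point, because the article names a model whose ordinary use does not suit these outcomes and states none of the three conditions that would make it suitable.

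Other parts of the reply also stand. The analysis is conditional on adjustment being needed, and the unadjusted relative risk and risk difference are untouched. Efron ties, exact ties and real event times are possible implementations, not things the article proposes. An adjusted risk difference is not expressly promised, and the Mantel-Haenszel method, which the article names for examining confounding, could yield a stratified one.

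A reader might also fix the excess at one narrow range, such as 33-61 %, by taking control rates of 40-55 %. The article gives no response rates, so it supports no such range. The rates its power statement needs at 150 per arm point to 57 % or more.

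**Conclusion.** The point holds as a conditional one. The named model does not match fixed-time binary outcomes, and only one unstated combination of settings makes it give the relative risk with a correct interval.

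The size depends on response rates the protocol article does not supply, so Step 4 is a range under assumption and not a property of the trial. The width ratio assumes equal arms. The power figure also assumes 150 analysed per arm, a two-sided 5 % level and no covariates, so it isolates the effect of the variance formula.

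A reader might infer that the trial's main comparisons are compromised or that false positives would follow. The document supports neither. The unadjusted comparisons stand, and under model-based variance with Breslow ties the point estimate remains the relative risk and the error is conservative. What is at stake is lost power and an apparent conflict between unadjusted and adjusted results on the primary outcomes. That is worth correcting before analysis.

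**What to change.** Replace the Cox sentence in Statistical analyses with:

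> Adjusted relative risks will be estimated by Poisson regression with robust (sandwich) variance (or log-binomial regression where it converges), and adjusted risk differences by standardisation from a regression model for the binary outcome.

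The cost is one sentence and minor extra analysis work; no new data are needed. Log-binomial and identity-link models may fail to converge, particularly when improvement is common, which is why robust Poisson regression should be the default.
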